### Allocation and blinding

Individuals will be randomly allocated to the intervention or control group. Participants will be block-randomised, stratified by gender, by the web-based randomisation service Sealed Envelope™ [33], overseen by a trial statistician uninvolved in data collection. Upon obtaining written consent, a research assistant will access Sealed Envelope™ to obtain the treatment allocation, and will therefore be aware of each participant’s allocation, but will be blind to the time point of psychometric assessments at the data analysis stage. Due to the nature of the intervention participants cannot assuredly be blinded to treatment, as they will be aware of the app they are using. The rest of the research team, including the principal investigator and clinical lead, will be blinded to the allocation of each family.

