### Procedure

Participant eligibility will be assessed by the clinical lead, and staff under her direction. Research assistants will ascertain consent, allocate participants according to an independent randomisation procedure (https://SealedEnvelope.com/), and administer assessments, including recording a 12-min video of child and parent in free play for later scoring with the DCMA and BOSCC. The Principal Investigator (PI) received formal training in DMCA and BOSCC coding, which he passed on to the research assistants. The research assistants are trained to a high standard in psychometric and qualitative administration and coding, and receive regular supervision from the PI, the clinical lead, and qualitative specialist. Members of the research team responsible for data collection have completed CPFT Good Clinical Practice training. Parents will receive training to deliver the intervention and will be asked to keep a diary. Parents will be asked to complete the optional think-aloud session and focus group.

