### Statistical analysis plan

Results will be analysed by the intention-to-treat principle. Guidelines and standard practices for each outcome measure will be used to impute values for missing items in individual datasets. For example, guidelines for the SRS-2 recommend using the median of the items answered. Any systematically missing subscales within feasibility candidate measures will inform the decision as to which measures would be carried forward to a full-scale RCT. This feasibility trial aims to determine the sample size for the full RCT. Test-retest variances in internal iPad data and external outcome measures will be entered into a standard calculation of statistical power to inform the sample size of a full RCT. Participant flow in terms of recruitment and retention, reported in line with the Consolidated Standards of Reporting Trials (CONSORT) statement for non-pharmacological interventions, will also inform the sample size for a large RCT. The trial statistician will perform the power and sample size calculations. Statistical analysis will be conducted in R.

We will explore the predictability of treatment effects based on the baseline measures. Findings may shed light on whether the intervention is more suited to certain profiles of autism than others. Inclusion criteria for a subsequent full trial would be fixed accordingly. Standardised scores from psychometric assessments will be analysed using mixed-model analysis of variance with time point (pre-intervention, post-intervention) as the within-subjects factor, and treatment (intervention, control) as the between-subjects factor. The internally logged outcome measures of visuomotor accuracy in Point OutWords will be analysed using three separate exploratory analyses of covariance, with Point OutWords usage time, number of distinct Point OutWords sessions, and real time as covariates. Participants’ own responses will be discriminated from caregivers’ model inputs by a statistical clustering method. Fidelity will be assayed using descriptive reports of content, and duration and number of intervention sessions completed.

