#### Auditing

Trial conduct will be audited monthly by the PI and the clinical lead. In accordance with Good Clinical Practice, a site folder will be held at the City Care Centre within the CPFT Integrated Children’s Service, containing copies of correspondence with families, the protocol, and a delegation log specifying the responsibilities of research team members. Case report forms for each participant will be used to record personal information, treatment allocation, dates of assessments and iPad drop-off, and relevant information collected during telephone calls during the intervention period e.g*.* if the child was feeling sick. Recruitment data are uploaded monthly to the NIHR Clinical Research Network Portfolio by a research assistant so that CPFT can provide additional support if the trial falls behind schedule.

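### No arm-masked tester is assigned for the post-intervention MSEL, BPVS-III and VMPAC, and the stated time-point masks cannot protect scores fixed at the visit

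*Protocol article*

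**What the plan says.** All references are to the protocol article.

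- **Allocation.** Under Allocation and blinding, "a research assistant will access Sealed Envelope™ to obtain the treatment allocation, and will therefore be aware of each participant’s allocation". The same sentence adds the only mask stated for that person: "but will be blind to the time point of psychometric assessments at the data analysis stage". The section closes with "The rest of the research team, including the principal investigator and clinical lead, will be blinded to the allocation of each family".
- **Who does what.** Under Procedure, "Research assistants will ascertain consent, allocate participants according to an independent randomisation procedure", and the same sentence goes on: "and administer assessments, including recording a 12-min video of child and parent in free play for later scoring with the DCMA and BOSCC". Consent, allocation and assessment thus belong to one staff role, and the play video is the only item set aside for later scoring.
- **Video coding.** The same rater codes a child's two recordings without knowing which visit each comes from. This rule covers the DCMA and BOSCC only.
- **The tests at issue.** Three MSEL subscales (fine motor, receptive language, expressive language) and the BPVS-III are listed under Primary outcomes, and the VMPAC under Secondary outcomes. Each entry plans a comparison of change between the arms.
- **Other routes to knowing the arm.** A research assistant trains the caregiver in the app (Background). The research team telephones families every fortnight about the assigned intervention (Adherence monitoring). Under Auditing, "Case report forms for each participant will be used to record personal information, treatment allocation, dates of assessments and iPad drop-off".

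**The concern.** A time-point mask applied at the analysis stage works only on material that is scored after the visit by someone who cannot tell which visit it came from. In a directly administered test, the prompting, the pass or fail calls and the decision to stop are made in the room. The tester knows that this is the post-intervention visit and may know the arm. Nothing done at analysis changes a score already on the form.

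Two consequences follow.

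1. An arm difference on the MSEL, BPVS-III or VMPAC could partly reflect the tester's expectation, although the MSEL entry says these differences will measure treatment efficacy.
2. The Background and Aims use this trial to choose measures sensitive to change for the full trial. A test open to expectancy may look more responsive than one coded from video under a mask, for reasons unrelated to the child.

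The order of randomisation and baseline testing does not settle this. Randomising after baseline would leave the post-intervention tests just as they are.

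**Working it through.** **Step 1: set the masks against the measures.**

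| Measure | How the score arises | Stated mask | Does the mask reach the score? |
|---|---|---|---|
| BOSCC, DCMA | Coded later from the play video | Time point | Yes |
| MSEL (three subscales), BPVS-III | Administered directly to the child | Time point, at analysis | No, if scored at the visit |
| VMPAC | Administered directly to the child | Time point, at analysis | No, if scored at the visit |

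Scoring at the visit is an inference. It rests on direct administration, on Procedure reserving later scoring for the video, and on the absence of any described recording or re-scoring of these tests.

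**Step 2: why the time-point mask is useful for video.** The analysis is a mixed model "with time point (pre-intervention, post-intervention) as the within-subjects factor" and treatment as the between-subjects factor, so the arm comparison is one of change. Suppose a coder knows the arm but not the visit and shifts that child's scores by b. The change becomes (post + b) − (pre + b) = post − pre, so b cancels. A tester who knows both arm and visit can shift the post-intervention score alone. The change is then (post + b) − pre, and b remains.

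**Step 3: size, for illustration.** The documents give no size for b, so it is assumed and shown as a range.

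Inputs: 23 per arm (Sample size), no true effect, two-sided 5% test, and b = d × SD of change, acting in favour of one arm.

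- Degrees of freedom: 23 + 23 − 2 = 44. Critical value: 2.015.
- Standard error of the standardised difference: √(2/23) = 0.295.
- Non-centrality: d / 0.295.
- Rejection rate: the probability that a non-central t with 44 degrees of freedom falls outside ±2.015.

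| Assumed shift d (SD) | Non-centrality | Rejection rate | Normal approximation |
|---|---|---|---|
| 0 | 0 | 5.0% | 5.0% |
| 0.2 | 0.68 | 10.2% | 10.4% |
| 0.3 | 1.02 | 16.9% | 17.4% |
| 0.4 | 1.36 | 26.4% | 27.4% |
| 0.5 | 1.70 | 38.2% | 39.6% |

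The rates are per score. Four primary scores are exposed (three MSEL subscales and the BPVS-III), plus the VMPAC.

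**Step 4: what this model leaves alone.** A constant shift within an arm moves that arm's mean change but not its SD. Under this model the variance passed to the full trial's sample-size calculation is unaffected. What is distorted is the apparent effect, and with it the apparent sensitivity to change. The protocol states no figure on this point to reproduce.

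**The case against.** **The text does not show that every tester knows the arm.** This stands. Allocation and blinding speaks of one research assistant obtaining the allocation and calls the rest of the team blinded, so a masked colleague could do the testing. A reader might infer that all post-intervention testers are unmasked, but the document does not support that. It supports only that no masked tester is assigned, while one role holds allocation, assessment and caregiver training. A delegation log is mentioned under Auditing and could settle who tests whom, but its content is not shown.

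**The time-point mask is not on the wrong label.** This stands for video. A reader might infer that it should be exchanged for an arm mask because time point is a factor in the model. A factor can be in the model and still be hidden from the coder, and step 2 shows that hiding it protects change scores. Removing it would weaken the BOSCC and DCMA.

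**This is a feasibility trial.** The Discussion says it is not scoped to establish effectiveness, so false-positive rates are not its main currency. This stands in part and lowers the stakes. The between-arm comparisons are nevertheless planned, and choosing sensitive measures is one of the stated aims.

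**The instruments are not equally exposed.** This stands. The VABS-2 is a parent interview and parents know which app they use, so a masked interviewer would help little; it is left out. BPVS-III answers are the child's own pointing, which may leave the tester less room than in the MSEL or VMPAC.

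**Conclusion.** The point holds as a gap in the assignment of testers. The only masks stated for the staff who test cannot reach MSEL, BPVS-III and VMPAC scores fixed at the visit, and no arm-masked tester is named for them. This rests on the inference that these tests are scored at the visit. Whether bias would occur, and how large it would be, is unknown: the range of about 10% to 38% follows from assumed shifts of 0.2 to 0.5 SD and is not an estimate. Since efficacy is not the primary aim, the main practical risk is to the choice of outcome measures for the full trial. The change is worth making because it is cheap, not because the trial's feasibility conclusions depend on it.

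**What to change.** 1. State that the post-intervention MSEL, BPVS-III and VMPAC are given by an existing research assistant who did not allocate, train or telephone that family and who has no access to its allocation record or case report form.
2. Ask families not to name the app at that visit, and record any unmasking.
3. If the existing team cannot do this, state that these measures are not assessor-masked, and weigh that when their sensitivity to change is compared with that of the video-coded measures.
4. Keep the time-point mask for video coding. Coding arm as A/B for the analysis may be added to it but must not replace it, and it would not protect scores already fixed at the visit.

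**Cost.** A few sentences of text and a rota change among the research assistants, whom Procedure mentions in the plural. Their number is not given, so item 3 is the fallback. The child meets a less familiar tester at the second visit, equally in both arms. Some unmasking may still occur, since testing can take place in the home where the iPad is used.

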### Intervention

Point OutWords [30] is an iPad game developed to train fine motor and cognitive skills in children with autism. Participants in the experimental group will receive the Point OutWords intervention, with a target of at least 20 h of contact time, as an adjunct to standard NHS clinical therapy. The intervention will be administered by parents/caregivers in the home, either on a loaned iPad or on the family’s own iPad if preferred. Parents will receive training from the research team to use Point OutWords, and written instructions.

Point OutWords has three modes of increasing difficulty, which tap skills prerequisite to language and communication. Learning starts in the Point mode where the child uses their finger to drag jigsaw pieces to complete a picture. The object is segmented into jigsaw puzzle pieces, which are scattered round the touchscreen. Puzzles are images from daily life e.g. bath, shampoo. The child has the opportunity to develop the manual motor skills prerequisite to pointing to interact with a touchscreen. The touchscreen software interface is adapted so as to accommodate the autistic user’s open-loop style of visuomotor control and is customisable to meet the child’s motor ability.

From here, the child progresses to Type mode. In Type mode, puzzle pieces cannot be dragged into place in an iconic style of reference, but instead must be cued by symbolic reference: Each puzzle piece is labelled with a letter in the word, there are as many puzzle pieces as there are letters in the word, and in order to cause a piece to snap into place within the puzzle, the participant must press the corresponding letter key on a virtual keyboard that appears on the touchscreen. The Type mode aims to encourage symbolic representation, with which non-verbal children with autism show difficulty [34] and which underpins communication development [35]. In addition to improving motor skills, Point OutWords teaches sequencing through piecing several parts of a puzzle together. Cognitive sequencing underlies language development along with planning for social interaction and daily activities [26].

Finally, in the Speak mode the child assembles each jigsaw piece by speaking each syllable of a word in order, allowing the child to practise their oral motor skills. The object is segmented into a number of puzzle pieces equal to the number of syllables in the word. Each syllable is modelled, the client is prompted to speak each one, and OpenEARS speech recognition software is used to detect these pronunciations. Speaking a syllable causes the corresponding puzzle piece to snap into place. Tolerance for articulation errors and other slight inaccuracies of the match between actual and modelled pronunciations can be configured by the caregiver. Advancing to Speak mode will be difficult for the majority of children in this non-verbal/minimally verbal sample; we expect that most children will stop with Type mode.

Point OutWords is intended to be used with a parent or other caregiver who can support the child in an “errorless learning” format, filling in responses and correcting errors when the child is unable to do so independently, and redirecting the child towards the task when attention wanders. Progressing to a more difficult level is at the discretion of the caregiver in interaction with the child.

### Control group

Participants not receiving the experimental intervention receive standard NHS clinical therapy and equal iPad contact time using a selection of iPad apps, which include Magic Fluid Lite [36], Heat Pad - Relaxing Heat Sensitive Surface! [37], Draw with Stars! Play With Shooting Stars [38], Baby Drum [39], Doodle Buddy Paint Draw App [40], Aquarium Live HD [41], and Dogs [42]. Control apps were chosen based on their absence of skill promotion, particularly in areas Point OutWords aims to enhance, such as sequencing, assembling puzzles, vocabulary learning, fine motor skills training, social learning, or skills that underpin language development (e.g. category learning). The control group will receive equal regular support during the study period, and will be offered Point OutWords intervention after the end of the study.

### Adherence monitoring

Participants will have fortnightly contact with the research team via telephone calls to monitor fidelity to assigned intervention, and address queries related to the intervention or using the app(s). During telephone calls, consent for continuing participation is taken or, on the participant’s request, the intervention is stopped. iPad data logged during sessions will be used to monitor session frequency, session length, and games played. Participants will be asked to keep a diary during the intervention period, which includes questions related to frequency of iPad sessions, when during the day iPad sessions take place, and the types of games played. Phone calls and diaries will also record what other interventions, if any, the child or parents are taking part in.

### Outcomes

#### Primary outcomes

##### Child observations

**Mullen Scales of Early Learning (MSEL)**

The MSEL [43] is widely used as a measure of cognitive ability, motor ability, and language skills in research and clinical evaluations of children with autism [44, 45]. Relevant to the study, the fine motor, receptive language, and expressive language subscales will be administered. Each subscale yields developmental age equivalents, and therefore is applicable to developmentally delayed children outside the 68-month normed age range [46]. The MSEL shows good test-retest and inter-rater reliability [43] and strong concurrent validity with other developmental tests of motor and language, including the Vineland Adaptive Behaviour Scales II (VABS-II) [44]. Differences in mean scores from baseline to post-intervention between the intervention and control group will measure treatment efficacy. Separately, baseline mean scores will be used to characterise for whom the treatment is (or might be) effective. For example, a disparity in age-equivalent scores between the receptive and expressive language domain might predict treatment effects.

**Brief Observation of Social Communication Change (BOSCC)**

The BOSCC [47] is scored from a 12-min video recording of a parent-child play session, coded on 16 items assessing atypicality, frequency, and severity of autistic symptoms. The BOSCC coding scheme was developed from the Autism Diagnostic Observation Schedule (ADOS)-2 [48] by the same research team, to detect clinically significant changes in autistic symptoms following treatment. The BOSCC has yielded excellent inter-rater reliability and high test-retest reliability [47]. Treatment efficacy will be measured by differences in mean scores from baseline to post-intervention between the intervention and control groups.

**Dyadic Communication Measure for Autism (DCMA)**

The DCMA [8] is coded from the same parent-child play session as the BOSCC, to assess dyadic communicative interaction between parent and child, making it largely complementary to the behaviours scored by the BOSCC. Independent codes are applied to instances of the parent’s synchronous responses with the child, the child’s initiations with the parent, and the time spent in shared attention. The mean change from baseline to post-intervention will be compared between the intervention and control groups.

**British Picture Vocabulary Scale III (BPVS-III)**

The BPVS [49] provides a rapid measure of receptive vocabulary, tested via the same method - nonverbal pointing - that Point OutWords applies in its Point Mode (and builds on in Type Mode). Inclusion of this measure thus aims to assess both vocabulary itself and the ability to express vocabulary through pointing. The mean change from baseline to post-intervention will be compared between the intervention and control groups.

##### Parent reports

**Social Responsiveness Scale II (SRS-2)**

The SRS [50] assesses social communicative competence from 2.5 years onwards. Comprising 65 items, the SRS-2 is sensitive to behavioural change and widely used as an autism treatment outcome measure [51, 52]. Mean scores taken at baseline and post-intervention will be compared between the intervention and the control groups.

##### Feasibility and acceptability measures

**Internal iPad data**

Pseudonymised activity logs will be uploaded from the iPad. A time series of all stimuli and responses, number of completed puzzles, and total and average session length will be logged.

**‘Think-aloud’ sessions**

An optional session in which parents are recorded voicing their thoughts and experiences whilst using Point OutWords, the individual “think-aloud” session will be completed before the intervention period begins.

**Focus groups**

An optional group interview will be held after participation in the study, for the intervention and control groups separately. Each interview group will comprise four to six parents/caregivers. The first part will be a group think-aloud session during which caregivers voice their thoughts and experiences whilst using Point OutWords, facilitated by a team comprising the research assistants who have worked with caregivers and their children, an autism parent member of the research team who is not a participant in the study, and an expert on qualitative data collection. Think-aloud methodology can provide a valid source of data on participants’ thinking [53]. The second part will be a group discussion, without the research assistants present, addressing the software, families’ experiences using it, and how it fits into their daily family routine.

**Clinician interviews**

Semi-structured interviews will take place post-intervention with four referring clinicians. Questions will address their views on the intervention and on recommending it to parents.

#### Secondary outcomes

##### Child observations

**Verbal Motor Production Assessment for Children (VMPAC)**

The VMPAC [54] assesses neuromotor integrity of the speech system and is standardised for ages 3–12 years [54]. Items are categorised into five subdomains: global motor control, focal oromotor control, sequencing, connected speech and language, and speech characteristics. The VMPAC is sensitive to change following speech or motor intervention [55, 56], and subtests have strong test-retest reliability (correlation .88–.90), inter-rater reliability (correlation .93–.99), and high validity [54]. It will be administered at baseline and post-intervention, and mean score differences will be compared between the intervention and control groups.

